### Secondary outcomes

6.2

1.Clinic blood pressure: This index is used to assist the observation of blood pressure change trend of patients. The same doctor will use the same blood pressure meter in the same period on the same day. The blood pressure will be measured with Omron brand blood pressure meter (HEM-8711). After 5 minutes’ rest in a quiet environment, the blood pressure of the patient's right upper arm will be measured. Measure twice and take the average value. If the difference between the 2 times is >5 mmHg, the average value of 3 times shall be taken.2.Hospital Anxiety and Depression Scale (HAD): HAD is composed of anxiety scale and depression scale. The highest score of HAD is 42. The higher the score is, the worse the mental state of the patients is. The total score of 0 to 7 is normal, 8 to 10 is mild, 11 to 14 is moderate, and 15 to 21 is serious anxiety/depression. The patients’ mental and emotional health will be evaluated by the HADs.3.Syndrome integral of HLY: This index is used to observe the changes of syndrome of patients. Referring to the symptom grading scale, the symptom grading scale of HLY will be formulated. The symptom grading scale is from the diagnostic and curative effect standard of traditional Chinese medicine (2017 Edition).^[7]^ The evaluation symptoms included dizziness, headache, irritability, blush, hot eyes, thirst, bitter taste, constipation, reddish urine, dysphoria in chestpalms-soles, tinnitus, insomnia, and lumbar debility. The highest score is 42, and the lowest score is 0. The higher the score, the more serious the symptom.

The secondary outcomes mentioned above will be evaluated in the first week (baseline period), the fifth week (after acupuncture period), and the seventh week (after follow-up period).

### Auxiliary outcomes

6.3

1.Blood pressure load: blood pressure load is the percentage of times that SBP and DBP readings exceed the normal range respectively. The normal standard is 24- hour ambulatory blood pressure <130/80 mmHg, daytime blood pressure <135/85 mmHg, and nighttime blood pressure <120/70 mmHg. It is generally considered that normal load should be <5%.2.Risk rate of salt sensitivity: In 2011, Italian scholars proposed that the risk rate of salt sensitivity can be preliminarily determined by the nighttime blood pressure drop rate (monitored by 24-hour ambulatory blood pressure) combined with 24-hour average heart rate.^[12]^ The specific assessment method: the blood pressure of the observed patients does not drop at night, that is, the patients with nondipper blood pressure. If their 24-hour heart rate is ≥70 beats/min, about 70% of them are salt sensitive in the saline infusion test, and define this type of patients as having high risk of salt sensitivity. Dipper blood pressure and 24-hour heart rate <70 beats/min are defined as low risk of salt sensitivity, whereas others are defined as medium risk of salt sensitivity.

The auxiliary outcomes mentioned above will be evaluated at the first week (baseline period) and the fifth week (after acupuncture period).

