### Inclusion criteria

3.3

1.Age: 18 to 65 years, both male and female;2.Met the Western diagnostic criteria of essential hypertension. For patients without antihypertensive drugs, SBP: 140 to 179 mmHg and/or DBP: 90 to 109 mmHg. For patients with antihypertensive drugs, hypertension should be stabilized at a normal high value. The patients who took medicine used ≤2 antihypertensive drugs for >2 months.3.Confirmed TCM diagnosis of HLY in hypertension.4.Not receives acupuncture or Chinese herbal medicine treatment in recent 1 month.5.Good compliance with the observation and evaluation of researchers.6.Informed consent is signed by the patient himself or his immediate family members.

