### Main outcome

6.1

Ambulatory blood pressure monitoring: 24 hours ambulatory blood pressure is the “criterion standard” to evaluate the antihypertensive effect.^[11]^ In this study, the 24 hours ambulatory blood pressure monitor (DMS-ABP) made by American Tim will be used for data collection. Ambulatory blood pressure will be measured in patients’ nondominant arm to reduce the impact of activity on blood pressure measurement. The detection time of each patient should be >23 hours. At the same time, the effective reading is >70%. There are at least 20 daytime blood pressure readings and 6 nighttime blood pressure readings.

Ambulatory blood pressure monitoring will be evaluated in the first week (baseline period), the fifth week (after acupuncture period), and the seventh week (after follow-up period).

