## Discussion

10

The hypertension patients included in this study are HLY, which accounted for a high proportion (24.1%) of hypertension patients.^[13]^ Therefore, it has important research significance. TCM believes that HLY belongs to a syndrome type of water failing to nourish wood, and deficiency in origin and excess in superficiality. Its pathogenesis is related to a series of pathological manifestations caused by the reverse ascending of Chong Channel in TCM. Therefore, Taichong (LR 3), Baihui (DU 20), Taixi (KI 3), Sanyinjiao (SP 6), and Zusanli (ST 36) are used as the main acupoints for adjustment. The purpose of these acupoints is to stabilize the reverse ascending of Chong Qi and guide the Qi downward. At the same time, these acupoints can also nourish yin to suppress yang, and regulate qi and blood. Finally, the goal of reducing blood pressure will be achieved. In addition, according to other symptoms and syndrome types of patients, matching acupoints will be selected to achieve better antihypertensive effect.

Our research group has been engaged in the research of twirling reinforcing reducing manipulation for a long time.^[14–15]^ Therefore, according to the theory of reinforcing deficiency and reducing excess, reinforcing and reducing manipulations on the main acupoints can achieve better therapeutic effect. The operation time of manipulation is 1 minute, and the time setting is in line with the clinical operation. The indicators of the research will be evaluated at most 3 times, and the scale is not large, so it will be collected smoothly. In addition, salt sensitivity of hypertension is common in China. Because it is difficult to popularize invasive saline infusion test on a large scale, clinical evaluation is difficult. Although the effectiveness of the salt-sensitive risk assessment method used in this study needs to be verified, it has good feasibility and promotion value. Therefore, it is worthy of further study.

This experiment focused on 1 type of hypertension. The highlight of the experimental design is to fix the main acupoints according to the characteristics of HLY, and select the matching acupoints according to patient's conditions. Therefore, it will be more effective in reducing blood pressure and is in line with clinical operation.

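### The salt-sensitivity risk class is scored before and after treatment as an efficacy outcome, yet a change in heart rate alone moves it and salt sensitivity is never measured

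*Protocol article*

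**What the plan says.** Section 6.3 (Auxiliary outcomes), within Section 6 (Efficacy index), takes over a published rule under which "the risk rate of salt sensitivity can be preliminarily determined by the nighttime blood pressure drop rate", combined with the mean 24-hour heart rate.

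- **High risk:** nondippers with a rate of 70 beats/min or more. The support offered is a cross-sectional share: "If their 24-hour heart rate is ≥70 beats/min, about 70% of them are salt sensitive in the saline infusion test".
- **Low risk:** "Dipper blood pressure and 24-hour heart rate <70 beats/min are defined as low risk of salt sensitivity".
- **Medium risk:** everyone else.

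The class is scored at week 1 (baseline) and week 5 (after acupuncture). The article describes no saline infusion test or other measure of salt handling in this trial. Section 10 (Discussion) calls the saline test invasive and hard to use widely, and concedes: "Although the effectiveness of the salt-sensitive risk assessment method used in this study needs to be verified".

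**The concern.** The rule was built to say, at one point in time, who is likely to be salt sensitive. Section 6.3 uses it for something else: to show what four weeks of treatment did. Nothing in the article supports reading a change of class as a change in salt sensitivity.

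One of the two inputs is heart rate with a hard cut. A nondipper whose mean rate goes from 71 to 69 beats/min moves from high to medium. A dipper with the same change moves from medium to low. Neither move needs any change in blood pressure or salt handling.

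If acupuncture slows the heart a little, the arms will differ in class, and the result will stand under the name of salt-sensitivity risk. Randomisation does not remove this, because the heart-rate effect would itself be a treatment effect, only under the wrong label. Two continuous measurements are also reduced to three classes in a trial of 56 patients.

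**Working it through.** **The plan's own figures.** The article gives no size or power figure for this outcome. Section 4.2 gives 23 per arm before dropout; 23 × 1.2 = 27.6, rounded up to 28 per arm, 56 in total, as stated.

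**Inputs from the article.** Heart-rate cut 70 beats/min; three classes as above; visits at weeks 1 and 5; recording minimum in Section 6.1: "There are at least 20 daytime blood pressure readings and 6 nighttime blood pressure readings".

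**Assumed inputs (not in the article).** Dipping cut at a 10% night-time fall. Daytime SBP 135 mmHg. SD of a single reading 10 or 12 mmHg. True night-time fall: mean 10%, between-patient SD 6 points. True 24-hour heart rate: mean 72, between-patient SD 8. Visit-to-visit heart-rate error: SD 3 or 5 beats/min.

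**Step 1: noise in the night-time fall.** Approximately, SE = 100 × √(SD²/night readings + SD²/day readings) / 135.
- 20 day and 6 night readings, SD 10: 100 × √(16.67 + 5.00) / 135 = 3.45 points.
- 20 day and 6 night readings, SD 12: 100 × √(24.0 + 7.2) / 135 = 4.14 points.
- Fuller recording, 40 day and 14 night readings (assumed), SD 10: 100 × √(7.14 + 2.50) / 135 = 2.30 points.

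**Step 2: class movement between visits.** Simulation of 1,000,000 patients per row. The middle column has no true change. The last three columns lower the true heart rate by 5 beats/min at week 5 and leave dipping alone. Net = lower − higher.

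| Readings; reading SD; heart-rate error | Switch class, no true change | To lower class | To higher class | Net |
|---|---|---|---|---|
| 20/6; 10; 3 | 33.2% | 30.0% | 9.6% | 20.4 |
| 20/6; 10; 5 | 38.6% | 30.5% | 12.0% | 18.5 |
| 20/6; 12; 3 | 35.7% | 30.8% | 10.8% | 20.0 |
| 20/6; 12; 5 | 40.7% | 31.2% | 13.0% | 18.2 |
| 40/14; 10; 3 | 28.0% | 28.3% | 7.2% | 21.1 |
| 40/14; 10; 3, with mean fall 6% and mean rate 76 | 23.3% | 26.0% | 6.1% | 19.9 |

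**Step 3: direction of the noise.** With no true change, movement is balanced: 16.6% down and 16.6% up in the first row, 20.4% down and 20.3% up in the fourth. The net is zero, and the same is expected in both randomised arms.

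**Step 4: a second set of assumptions.** Mean rate 70 or 74 (between-patient SD 9), mean fall 9% (SD 6), visit-to-visit SD 3 to 5 for each. Switching with no true change is 29% to 42%. The net downward shift for 5 beats/min is 16 to 19 points.

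**Step 5: power of a class comparison.** At 23 per arm and two-sided 0.05, power for a difference in the high-risk share is 20% for 35% against 20%, 31% for 40% against 20%, and 53% for 35% against 10% (assumed rates).

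**The case against.** The authors do not hide the limitation. They call the determination preliminary, say the method needs verification, rank the outcome below the primary and secondary ones, and nowhere say that a shift in class will be presented as a reduction in salt sensitivity. All of this stands and limits the weight of the point. It does not change the use in Section 6.3, where the class is still an efficacy index scored before and after treatment.

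Four stronger readings are tempting, and the article does not support them.

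- **Noise produces a false benefit.** It does not in the randomised comparison: the switching is symmetric and expected to be equal in the two arms, so it only dilutes. The minimum of 20 and 6 readings is also a validity floor, not the typical recording; a fuller recording with means away from the cut-offs brings switching down to 23%.
- **Rate-slowing drugs move patients between classes.** Entry sets a duration for treated patients: "The patients who took medicine used ≤2 antihypertensive drugs for >2 months". A stable drug sets the class at both visits and moves nobody. Movement would need a drug started or changed between weeks 1 and 5. Section 5.2 keeps the control arm's original treatment unchanged. Section 5.1 does not repeat that for the acupuncture arm, and untreated patients may enter, so a change is possible, but the article does not show that it will happen.
- **The dipping definition contradicts itself.** The phrase "the blood pressure of the observed patients does not drop at night, that is, the patients with nondipper blood pressure" is loose and gives no numeric cut. It reads as a gloss on a named category, and the cut may stand in the full protocol or in the cited method. It is absent detail, not an error.
- **Salt sensitivity will not have changed.** That cannot be known either. The class simply cannot separate the two explanations.

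**Conclusion.** The point holds in limited form, as a minor one. An unverified screening class serves as a before-after efficacy outcome without any measure of the thing it is named after, and a change in one input, heart rate, is enough to move it. A 5 beats/min slowing confined to one arm would give a net downward shift of about 18 to 21 points, or 16 to 19 under the second set of assumptions. Random switching of 23% to 41% (up to 42% under the second set) costs power in a comparison that has little to begin with.

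All these percentages rest on assumed means, SDs and a 10% dipping cut, none of which the article gives. The 5 beats/min is an illustration, not an expected effect of acupuncture. What does not depend on those assumptions is the structure of the rule: crossing 70 beats/min changes the class whatever happens to salt handling. The primary outcome and the sample size are unaffected.

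**What to change.** In Section 6.3:

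1. Use the salt-sensitivity class at week 1 only, as a baseline descriptor.
2. Replace it as an outcome with two continuous measures from the same ambulatory recording, the percentage night-time SBP fall and the 24-hour heart rate. Compare each between arms at week 5, adjusted for its baseline value.
3. State that no conclusion about changed salt sensitivity will be drawn.

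The cost is wording only: the existing rule already requires both measures, so nothing new is collected. The downside is that a change in the risk rate is no longer reported as an efficacy result.

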### Exploratory indicators

6.4

Acupoint diagnosis: all patients will be given acupoint diagnosis. Diagnostic acupoints: acupoints with 12 meridians below elbow and knee joint (1 cm around acupoints). In addition, there are some back shu points, including Ganshu (BL 18), Danshu (BL 19), Xinshu (BL 15), Pishu (BL 20), Weishu (BL 21), and Shenshu (BL 23) (1 cm around the points).

Specific diagnosis methods (traditional manual detection): slide the thumb pulp within 1 cm of the acupoint, ① Feel the abnormal reaction of the skin and the superficial part of the acupoint with light strength; ② Detect the abnormal performance of the muscle with medium strength, including streak, tubercle, bulge, and hollow; ③ Detect the abnormal reaction of the deeper layer with slightly heavy strength; ④ Apply the force evenly, and review repeatedly, then record the results. The acupoints with positive reaction and their specific conditions will be recorded. Then the pain degree will be evaluated by the international commonly used visual analogue scale (VAS), and the VAS score will be recorded. The acupoint diagnosis will conducted be in the first week (baseline period) and the fifth week (after acupuncture period) of the eligible participants.

### Safety indicators

6.5

#### Safety assessment

6.5.1

The experiment will observe the adverse events of the participants during the experiment (including acupuncture related events such as bleeding, hematoma, pain of acupuncture site, fainting during acupuncture treatment, high blood pressure, among others, and nonacupuncture-related events such as cold, cough, aggravation of pre-existing diseases, and so on). And fill in the adverse event report form (record time, location, symptom, degree, duration, treatment method, treatment result, among others, and sign the name and date). At the end of the treatment, the causes of each event will be analyzed and summarized carefully.

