**Methods::**

In this randomized controlled trial, we will recruit 56 hypertensive patients with hyperactivity of liver yang. Then the patients will be randomly divided into control group and experimental group. The control group will be treated with western medicine, and the experimental group will be treated with medicine combined with acupuncture. The intervention will last 4 weeks. The indices will be collected before acupuncture, after acupuncture, and 2 weeks after acupuncture. The primary outcome will be 24-hour ambulatory blood pressure. The secondary outcomes will be clinic blood pressure, anxiety and depression score, and the syndrome score of hyperactivity of liver yang. The auxiliary indicators will be blood pressure load values and salt sensitivity risk rate. The exploratory indicator will be acupoint diagnosis. The safety evaluation indicator will be incidence of adverse events.

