### Implementation of blind method

4.3

Due to the particularity of acupuncture clinical operation, this study will adopt a single-blind method, so only the efficacy evaluators and data statisticians will be blinded.

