### Acupuncture group

5.1

This group of patients will receive Western medicine treatment (each patient's specific medication should follow the advice of cardiovascular doctors), and will also receive acupuncture treatment at the same time. Record the type, dose, and frequency of drugs taken by each patient. The frequency of acupuncture will be once a day, 30 minutes each time, 5 times a week (2 days off), a total of 4 weeks.

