### Treatment plan of control group

5.2

The patients in the control group will be treated with antihypertensive drugs of western medicine, without changing the original western medicine treatment (the specific medication of each patient should follow the advice of cardiovascular specialist). And the patients will be instructed to take medicine regularly.

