## Statistical analysis

9

SPSS 20.0 statistical software will be used for data statistics (SPSS Inc, Chicago, IL). The frequency percentage will be used to describe the demographic data. For the measurement data with normal distribution and homogeneous variance, mean ± standard deviation (\bar{x} (Latex code) ± s) will used to describe the data. Paired and independent sample *t* test will used for intragroup and intergroup comparison respectively. For the measurement data of non-normal distribution, nonparametric test will be used. The blood pressure value will be analyzed by repeated measurement analysis of variance. In the correlation analysis of 2 theoretically related continuous variables, Pearson correlation coefficient model will be used if the data meet the normal distribution, and Spearman correlation coefficient model will be used if the data are nonnormal distribution. *χ*^2^ test will be used for counting data. All tests will be bilateral; *P* < .05 means the difference is statistically significant. In the correlation analysis, 0 < R≤0.2 means that there is no correlation between variables; 0.2<R≤0.4 means that there is a low correlation between variables; 0.4<R≤0.8 means that there is a moderate correlation between variables; 0.8 < R≤1 means that there is a high correlation between variables.

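### Contact is far more frequent in the acupuncture arm and no common adverse event enquiry is stated, so a crude between-arm comparison of incidence is open to detection bias

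*Protocol article*

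**What the plan says.** The abstract names a single safety measure: "The safety evaluation indicator will be incidence of adverse events". Section 6.5.1 says how events are gathered: "The experiment will observe the adverse events of the participants during the experiment". They are then entered on a report form. The section covers needling events and also "nonacupuncture-related events such as cold, cough, aggravation of pre-existing diseases, and so on". It gives no interval, no prompted question and no separate procedure for controls.

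The two arms have different contact schedules. Section 5.1 sets acupuncture at "5 times a week (2 days off), a total of 4 weeks". Section 5.2 keeps controls on their existing drugs and adds only this: "And the patients will be instructed to take medicine regularly". The assessments shared by both arms are placed in section 6.1 at "the first week (baseline period), the fifth week (after acupuncture period), and the seventh week (after follow-up period"), and section 6.2 uses the same weeks.

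On blinding, section 4.3 says that "only the efficacy evaluators and data statisticians will be blinded". Patients and acupuncturists therefore know the allocation, and section 6.5.1 does not assign event collection to a blinded role. Section 9 names no test for adverse events, although its general rule that the χ² "test will be used for counting data" would cover their incidence.

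**The concern.** When events are picked up by observation, the number recorded depends on how often someone is there to observe. A mild cold in week 2 is likely to be mentioned to an acupuncturist seen five days a week. The same cold in a control patient may never reach the form. Patients also know their treatment, which may affect what they mention.

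Safety is one half of the aim stated in the Introduction, and the Discussion part of the abstract promises evidence on it. A higher recorded incidence under acupuncture could reflect nothing more than closer contact. Similar recorded incidence could conceal more events among controls. Ascertainment cannot be repaired once the data are in, so the point is worth settling before recruitment is far advanced.

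**Working it through.** **Inputs from the protocol article.** 5 sessions a week for 4 weeks (section 5.1). Common assessments in weeks 1, 5 and 7 (sections 6.1 and 6.2). No control contact stated between weeks 1 and 5 (section 5.2). 1:1 allocation (section 2.1) of 56 patients (section 4.2), so 56 / 2 = 28 per arm. Two-sided testing at 0.05 (section 9).

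**Stated contacts, counting each assessment week as one.**

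| Period | Acupuncture | Control |
|---|---|---|
| Between the week 1 and week 5 assessments | 5 x 4 = 20 | 0 |
| All post-baseline | 20 + 2 = 22 | 2 |
| Including baseline | 20 + 3 = 23 | 3 |

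**From contacts to recorded incidence.** Recorded incidence = true incidence x share of events recorded. If true incidence is the same in both arms, it cancels, and the recorded risk ratio is simply the ratio of the two shares recorded. With equal shares it is 1.0.

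**Illustration, by assumption.** The article gives no adverse event rates and no recording rates. Assume the same true incidence in both arms, somewhere from 10% to 40%, with 90% of events recorded under acupuncture and 70%, 50% or 30% in controls. The last column is the probability of a significant result at 28 per arm, by the normal approximation.

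| Share recorded in controls | Recorded risk ratio | Recorded rates at 20% true incidence | Probability of a significant result (true incidence 10% to 40%) |
|---|---|---|---|
| 70% | 0.90 / 0.70 = 1.29 | 18% v 14% | about 5% to 9% |
| 50% | 0.90 / 0.50 = 1.80 | 18% v 10% | about 8% to 26% |
| 30% | 0.90 / 0.30 = 3.00 | 18% v 6% | about 15% to 56% |

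The true risk ratio is 1 in every row. The table shows the direction of the bias and how strongly it depends on the assumed shares. It does not estimate what will happen in this trial. With a mild imbalance the false-positive rate barely moves from the nominal 5%, so the main effect would be on the reported rates rather than on the test.

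**The case against.** The strongest reply is that this is a condensed article. The full protocol or the case report form may set calls, diaries or a standard enquiry at the common visits, and silence about these is no error. This stands against two stronger readings. A reader might infer that controls have no scheduled contact at all, or that their events are gathered by recall after about four weeks. The article says neither. It only states no such contact and no method. The reply does not remove the point, because the 20 sessions are stated design, and so is open observation of events that either arm can have. Section 7 lists the trial's measures against bias and none of them concerns event ascertainment.

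Second, a reader might infer that adverse events cannot be compared between arms. That goes too far. Both arms attend in weeks 5 and 7, so events elicited identically there can be compared. Serious events are also less likely to depend on how often a patient is seen.

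Third, no between-arm test of adverse events is named, and needling events can arise only in the acupuncture arm, so they are descriptive whatever the schedule. This is correct. It limits the point to a comparison of overall incidence, if one is made.

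Fourth, worsening among controls is not simply lost. Ambulatory and clinic blood pressure, the anxiety and depression scale and the syndrome score are taken in both arms at weeks 5 and 7, so deterioration present at those visits is measured equally. This also stands.

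Finally, unequal contact is inherent in adding acupuncture to usual drugs. That is true of contact. It need not be true of how events are elicited.

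**Conclusion.** The concern holds in a limited form. The acupuncture arm has 20 sessions in a period for which the article states no control contact, and events common to both arms are collected by observation with no stated common enquiry. A crude between-arm comparison of incidence is therefore open to detection bias, most likely against acupuncture. The contact imbalance (20 against 0 between weeks 1 and 5; 22 against 2 after baseline) follows from the text. The size of the bias does not, and the risk ratios of 1.29 to 3.00 merely restate the assumed recording shares.

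The conclusion assumes that more contact means more recording, and that no equal enquiry exists in a fuller document. If one does, the article need only say so. The primary outcome is not affected.

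**What to change.** In section 6.5.1:

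1. At the existing week 5 and week 7 visits, put the same short adverse event checklist, with the same recall window, to both arms.
2. Ask it after blood pressure and all other outcome measurements are complete, or have it asked by staff other than the blinded efficacy evaluator. Otherwise an answer about needling could reveal the allocation.
3. Base any between-arm incidence only on events elicited this way, plus serious events.
4. Report events noted at sessions, and needling events (bleeding, hematoma, site pain, fainting), separately as a descriptive acupuncture-arm rate per patient and per session.

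Identical brief telephone queries in both arms between visits would shorten the recall period, but they are optional.

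The cost is one short form and slightly longer visits. The comparison is then restricted to queried events, and mild events forgotten by week 5 will be missed, though with the same opportunity for report in both arms. No treatment or visit schedule changes.
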